## Abstract

**Background:**

Coronary microvascular disease (CMVD) can be described as one of the cardiovascular diseases with normal coronary angiography but evidence of myocardial ischemia or microcirculatory lesions, often presenting as angina pectoris attacks. Coronary artery microtubular dysfunction is one of the pathogenic features of coronary heart disease, but its occurrence and development and the current CMVD-intervention therapy needs further research. Chinese traditional medicine (TCM) has advantages for the treatment of cardiovascular diseases. Hence, this article describes an ongoing randomized controlled clinical trial based on the theory of TCM for the purpose of evaluating the efficacy and safety of *Guhong* injection versus placebo in patients with CMVD.

**Methods/design:**

This is a multicenter, randomized, parallel-arm, open-label, double-blind, placebo-controlled clinical trial. A total of 260 eligible patients will be allocated and randomly assigned, in a ratio of 1:1, to either the experimental group or the control group. The treatment course is 10 consecutive days, and with an 8-week follow-up. The primary outcome is therapeutic efficacy. Secondary outcomes include the quantitative score of TCM syndromes (a series of TCM symptoms and signs of coronary heart disease), the average frequency of anginal attacks, electrocardiogram (ECG) changes, inflammatory response, endothelial function indicators and myocardial metabolites.

**Discussion:**

This trial is strictly designed in accordance with principles and regulations issued by the China Food and Drug Administration (CFDA). The results should provide high-quality evidence on the efficacy and safety of *Guhong* injection in the treatment of CMVD.

**Trial registration:**

Chinese Clinical Trials Registry, ID: ChiCTR1900022902. Registered on 27 April 2019.

## Background

Coronary microvascular disease (CMVD) is a clinical syndrome with objective evidence of exertional angina or myocardial ischemia caused by structural or functional abnormalities of the precoronary arteries and arterioles under the influence of multiple pathogenic factors. In the past 20 years, a large number of studies have shown that coronary microcirculatory structural and functional abnormalities can be found in non-occlusive coronary artery diseases, but also in people with high risk factors for coronary heart disease, as well as in cardiomyopathic and occlusive coronary artery diseases, which have important predictive and therapeutic target values [1, 2]. Currently, there are still no large-sample epidemiological data on CMVD, but some clinical studies with small samples have shown that the incidence of CMVD is up to 45–60% in patients with myocardial ischemic symptoms but coronary angiography showing non-obstructive lesions, and the major cardiovascular events and all-cause mortality in these patients are significantly higher than in the control group [3]. It is currently generally believed that the pathogenesis of CMVD is complex. Endothelial injury, inflammatory factors, various vascular substances and microembolism may all lead to changes in microvascular structure and function, and the pathophysiological mechanism of different types of CMVD varies in clinical practice [4–6]. At present, treatment regimens using western medicine mainly include anti-thrombotic agents, lipid regulation, plaque stabilization and vascular dilation, etc., but these methods are not always successful and improved treatment remains an urgent problem to be addressed in clinical practice [7], Many patients still have repeated anginal attacks under the current drug treatment regimen, causing psychological anxiety and restlessness, which has a great impact on life and work.

TCM has the advantage of its multi-target and multi-link therapeutic effects and less adverse reactions than western therapies, especially for the treatment of cardiovascular and cerebrovascular diseases, and also has a long history and has been widely studied and its benefits confirmed. TCM treatment depends on different pathogenic mechanisms of disease but blood stasis is generally considered as one of the most important for coronary heart disease, so promoting blood circulation and removing blood stasis is an extremely important treatment goal [8]. In recent years, TCM research in the prevention and treatment of CMVD has shown good application prospects, but this is still not universally agreed treatment.

Redflower is one of the most famous TCM and is considered to be essential for promoting blood circulation and removing blood stasis [9]. *Guhong* injection is made with redflower extracts and acetylglutamide; of them, redflower extracts contain active ingredients such as redflower glycosides and redflower yellow pigment (Table 1). Clinical pharmacology research results show that *Guhong* injection can inhibit platelet aggregation, prevent thrombosis, cause expansion of the coronary arteries, reduce myocardial oxygen consumption, improve myocardial microcirculation, alleviate ischemia-reperfusion injury, and reduce anti-oxygen free radicals [10]. Accordingly, this study intends to use *Guhong* injection by peripheral intravenous drip as the treatment of CMVD to demonstrate its efficacy and safety, and to explore its mechanism of action from the perspective of the inflammatory response and endothelial function, so as to provide a basis for the treatment of coronary artery microvascular dysfunction using integrated TCM and western medicine.

**Table 1 Tab1:** Pharmacological effects of each ingredient in *Guhong* injection

Ingredient	Pharmacological effects
Redflower glycosides	Resist myocardial ischemia, resist platelet aggregation
Redflower yellow pigment	Protect heart muscle, resist oxidation, resist inflammation
Acetylglutamide	Activate nerve cell

## Methods/design

### Study design

This study is a multicenter, parallel, prospective, double-blind, randomized, placebo-controlled clinical trial. A total of 260 patients will be enrolled and randomly divided into the treatment and placebo groups. All patients will receive 10 consecutive days of treatment and follow-up for 8 weeks. Efficacy and safety data will be collected throughout the study. The study flow chart is shown in Fig. 1.

**Fig. 1 Fig1:**
[figure not shown]
Study flow chart. *ICF* informed consent form

### Ethics

This trial has been successfully registered in the China Clinical Trial Registry (ID: ChiCTR1900022902). Additionally, the study will be strictly conducted in accordance with the Helsinki Declaration, Good Clinical Practice (GCP) guidelines and national laws. The research protocol, informed consent, and recruitment posters were reviewed and approved by the Ethics Committee of the Guangdong Provincial Hospital of Traditional Chinese Medicine (No. BF2018–180-01). The researchers in all six trial centers are well-trained and qualified medical staff. All eligible patients will be fully informed and understand about this protocol and will sign an informed consent form (ICF) prior to participation. All participants can receive all examinations and treatments for free, and their privacy, data and security will be securely protected.

### Participants and recruitment

We will recruit patients who meet the criteria for inclusion by advertising on hospital notice boards, posting recruitment information in network communication groups or by being recommended by outpatient and inpatient physicians. A total of 260 eligible participants will be recruited in the following six hospitals: (1) Guangdong Provincial Hospital of Traditional Chinese Medicine, (2) Guizhou Provincial Hospital of Traditional Chinese Medicine, (3) Second Affiliated Hospital of Guizhou University of Traditional Chinese Medicine, (4) Foshan Traditional Chinese Medicine Hospital, (5) Shenzhen Longgang District Hospital of Traditional Chinese Medicine and (6) Yangjiang People’s Hospital. These six trial centers are all first-class hospitals in China, with advanced cardiovascular interventional departments, excellent medical teams and many inpatient beds. Especially the Guangdong Provincial Hospital of Traditional Chinese Medicine, which has the largest number of outpatients among the TCM hospitals in China and rich experience and achievements in the research of integrated Chinese and western medicine. So, the first center will recruit 80 patients, with 36 for each of the remaining centers.

### Inclusion criteria

For inclusion, participants should fulfill all the following criteria:
Coronary angiography or coronary computed tomography (CT) indicating the absence of unstable plaques, or coronary stenosis < 50% and the presence of clinical symptoms of stable angina pectoris [11].Aged between 35 and 75 years, regardless of genderWillingness to participate in the trial and to sign the ICF, with high degree of compliance and a cooperative attitude

### Exclusion criteria

Participants with any of the following conditions will be excluded:
Significant psychopathology, pregnant or lactating womenPatients with a history of myocardial infarction, heart failure, stroke, arterial dissection, arterial embolization, tumors, severe hematologic diseases, endocrine diseases or pneumonia and other infectionsPatients with liver and kidney dysfunction (expression of aminotransferase (ALT) and aspartate aminotransferase (AST) of 1.5 times higher than the normal upper limit, abnormal serum creatinine, positive urinary protein qualitative test)Patients who are allergic to *Guhong* injectionParticipation in other clinical trials and using the actual experimental drugs within the preceding 3 monthsPatients who are not considered by the researchers to meet the inclusion criteria

### Withdrawal criteria

The withdrawal criteria include the following:
Experiencing serious complications or rapid deterioration of the condition during the trial, including anginal attack frequency increasing significantly, myocardial ischemia continuing to worsen, myocardial infarction, arrhythmia and other changesSerious adverse events occurring, which should lead to treatment being stopped according to the physician’s judgmentParticipants with important deviations in the implementation of the program, such as poor compliance and difficulty in evaluating drug effectsQuitting the clinical trial voluntarily

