### Emergency unblinding

If an emergency occurs, the patient group assignment should be unblinded and known to the drug administrators or dispensing nurses, and corresponding emergency measures will be taken. Researchers will report this special situation to the center’s principal within 24 h. At the same time, the cause of unblinding, the time of the emergency, the solution and the result must be filled in the case report form (CRF). Once the participant ‘s allocated intervention during the trials has been revealed, the case will be withdrawn and the data will be recorded on day 10 of the trial evaluation.

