### Interventions

On the basis of conventional western medicine treatment, the *Guhong* group will be given a 20-ml intravenous infusion of *Guhong* injection that was diluted with 250 ml 0.9% sodium chloride injection once a day, while the control group will be given 270 ml 0.9% sodium chloride injection as placebo treatment once a day. (*Guhong* injection is provided by China tonghua guhong pharmaceutical co. Ltd. The production batch number is 20190306 and each bottle has a capacity of 5 ml. The drug distributed to each center will be labeled with the statement “for trial only” and the information of the name, dosage, dosing plan, indications, storage conditions, expiratory date, manufacturer and so on. Each center has an independent manager responsible for receiving, handling, storing and distributing the medications.) The course of treatment is 10 days. On the day of enrollment and at the end of treatment, the clinical symptoms and signs of angina pectoris will be recorded, the quantitative table of TCM syndrome will be scored, the electrocardiogram (ECG) will be examined, and the indicators of inflammation, endothelial function, myocardial metabolites and related biochemical tests will be conducted. Moreover, patients will be followed up for 8 weeks after the end of treatment, including any improvement in angina pectoris and the TCM syndrome quantitative score. During the entire study period, participants will be visited for a total of four times by the investigators. Specific research process details are provided in Table 2.

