### Efficacy assessment

#### Primary outcome

The criteria for therapeutic efficiency evaluation is based on the principles for clinical research reports on cardiovascular drugs formulated by the National Health and Pharmaceutical Bureau of China [13] by comparing the anginal attack frequency and ECG changes before and after treatment in the two groups of participants. Specific evaluation criteria are shown in Table 3.

**Table 3 Tab3:** Evaluation criteria on the therapeutic efficiency

Three-graded criteria	Detailed description	Classification
Significant improvement	Anginal attacks disappeared or significantly improved, decreased by 80%; electrocardiogram (ECG) returned to normal or substantially normal	Significantly effective
Improvement	Anginal attacks improved or the frequency of anginal attacks decreased by 50–80%; the descending ST segment of the ECG rose ≥ 0.05 mV, and the ascending ST segment fell ≥ 0.05 mV, but still did not return to normal; or the T wave of the main ECG lead changed from flat to upright; or the T wave changed from inverted to shallow by more than 50%	Effective
No improvement	No change or even aggravation of anginal attacks, no decrease or even increase of the frequency of angina pectoris attacks, no change or even aggravation of ECG ST-T segment	No effect

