#### The average frequency of angina pectoris

The average frequency of angina pectoris from the first day of enrollment to the end of treatment and at 8 weeks of follow-up will be recorded in the CRF. Each participant will be instructed to record any change in their symptoms of angina pectoris in their patient diary daily.

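### The withdrawal rule is not limited to the 10-day course and is triggered by worsening angina, so week-8 angina and TCM scores would probably be missing for patients who deteriorate markedly

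*Protocol article*

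**What the plan says.** The first item under Withdrawal criteria reads: "Experiencing serious complications or rapid deterioration of the condition during the trial, including anginal attack frequency increasing significantly". It goes on to name worsening ischaemia, infarction and arrhythmia. Of the four items, only the one on serious adverse events mentions stopping treatment. The last item is the participant's own choice to leave the trial.

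Study design sets the period: "All patients will receive 10 consecutive days of treatment and follow-up for 8 weeks". Interventions says what the second part is for: "patients will be followed up for 8 weeks after the end of treatment, including any improvement in angina pectoris and the TCM syndrome quantitative score".

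Anginal frequency is a secondary outcome with two time points, in the subsection of that name: "The average frequency of angina pectoris from the first day of enrollment to the end of treatment and at 8 weeks of follow-up". The primary outcome is assessed earlier, "by comparing the anginal attack frequency and ECG changes before and after treatment in the two groups of participants".

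Two other sections say what happens to data when a patient leaves. After emergency unblinding, "the case will be withdrawn and the data will be recorded on day 10 of the trial evaluation". After use of a prohibited drug, Concomitant treatments and forbidden drugs removes the patient and does not use the data. Withdrawal criteria gives no data consequence.

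**The concern.** A withdrawal rule is usually there to protect a patient by stopping study treatment. Here treatment ends at day 10, but the rule is worded to cover the whole trial. During follow-up it has no infusion to act on, and its only possible effect is on whether the patient goes on being observed. What triggers it is a marked rise in the same quantity that follow-up is meant to measure.

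If observation stops at that point, the patients missing at week 8 are those who did worst, and the values are missing because of the outcome. The week-8 angina frequency and TCM score are the trial's only information on whether a 10-day course has a lasting effect, or whether symptoms return or rebound afterwards. An analysis of the patients who remain would say little about either. Later analysis could not put this right without untestable assumptions, because the values would never have been collected.

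**Working it through.** The plan gives no figure on this point, so there is nothing to reproduce. The check has two parts: reading the sections together, and an illustration with assumed relapse rates.

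**Reading the sections together**

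1. *Scope.* Withdrawal criteria refers to the trial, not to treatment. Study design and Interventions make the 8 weeks part of the trial. The rule therefore reaches follow-up.
2. *Trigger.* The rule names a significant rise in attack frequency, with no threshold. Attack frequency is an outcome at the end of treatment and at week 8. The trigger and the outcome overlap.
3. *Effect after day 10.* All infusions have been given, so only observation can end.
4. *Data after withdrawal.* The section is silent. Three things point to loss: the same list includes participants who choose to leave the trial; the two sections that do state a consequence either mention data only at day 10 or discard the data; and no section keeps a withdrawn patient in follow-up.
5. *Analysis set.* A patient who completes 10 days and then deteriorates still meets the article's definition of the full analysis set. Membership does not supply a week-8 value that was not collected.

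**Illustration**

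Inputs from the document (Sample size): response of 81.82% with control and 93.94% with Guhong, used here as day-10 response. Assumptions of mine: a share *r* of each arm relapses in follow-up, only responders relapse, and every relapser is withdrawn and drops out of the week-8 denominator. The last assumption is the extreme case. With day-10 response *s*:

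- true week-8 response = *s* − *r*
- observed week-8 response = (*s* − *r*)/(1 − *r*)
- overstatement in that arm = *r*(*s* − *r*)/(1 − *r*), which is never negative

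For *r* = 15% in control and 5% in Guhong:

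- Control: true 0.8182 − 0.15 = 0.6682; observed 0.6682/0.85 = 0.7861.
- Guhong: true 0.9394 − 0.05 = 0.8894; observed 0.8894/0.95 = 0.9362.
- Difference: true 0.2212; observed 0.1501.

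The other rows follow the same steps.

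| Relapse, control / Guhong (assumed) | Control, true → observed | Guhong, true → observed | Difference in points, true → observed |
|---|---|---|---|
| 10% / 5% | 71.8% → 79.8% | 88.9% → 93.6% | 17.1 → 13.8 |
| 15% / 5% | 66.8% → 78.6% | 88.9% → 93.6% | 22.1 → 15.0 |
| 20% / 10% | 61.8% → 77.3% | 83.9% → 93.3% | 22.1 → 16.0 |
| 10% / 10% | 71.8% → 79.8% | 83.9% → 93.3% | 12.1 → 13.5 |
| 5% / 15% | 76.8% → 80.9% | 78.9% → 92.9% | 2.1 → 12.0 |

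In the last row Guhong patients relapse more often: 0.7682/0.95 = 0.8086 and 0.7894/0.85 = 0.9287. Week-8 response is overstated in both arms in every row. The difference is understated in the first three rows and overstated in the last two.

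**The case against.** The strongest reply is that the article does not say these patients are lost. Withdrawal criteria lists triggers and no data consequence. Where the authors mean to discard data they say so, as for prohibited drugs, and for unblinded cases they keep a record. A condensed article may also leave visits after withdrawal to the full protocol, and its schedule (Table 2) and flow chart (Fig. 1) could not be read in the text used here. This stands in part: loss of week-8 data is an inference, not a stated rule. It remains the natural inference, for the reasons given in the working. A rule that withdraws patients on an outcome, throughout the outcome period, is also more than an omitted detail.

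Four stronger readings are tempting, and the documents do not support them.

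- *Every patient who relapses is withdrawn.* The trigger is serious complications or rapid deterioration. A patient whose angina drifts back to its baseline rate need not meet it. The table removes every relapser and so shows an extreme.
- *A real difference would vanish.* One can build such a case. With 15% and 5% relapsing at 8 attacks a week and everyone else at 2, the true means are 0.15 × 8 + 0.85 × 2 = 2.9 and 0.05 × 8 + 0.95 × 2 = 2.3. With relapsers removed, both are 2.0. The zero follows from giving all remaining patients the same value. It is not a general result.
- *The primary outcome is affected.* It compares before with after treatment, and withdrawal after day 10 cannot change it. Withdrawal before day 10 raises a separate question about the 10-day dosing condition in the full analysis set, and adds no weight to the follow-up point.
- *Unblinded patients are treated better.* Someone who deteriorates in follow-up has already had the day-10 assessment, and Emergency unblinding promises no week-8 record either.

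The daily diary softens the problem somewhat, since worsening should be recorded up to the point of withdrawal. It does not give the week-8 value.

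**Conclusion.** The point holds in a limited form and is of moderate weight. Firm from the text: the withdrawal rule is not confined to the 10 days, its trigger overlaps with a follow-up outcome, how much worsening counts is left undefined, and nothing says that withdrawn patients stay under observation. Inferred: week-8 angina and TCM-score values would be missing for patients who deteriorate markedly after day 10.

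On that inference missingness depends on the outcome, both arms look better at week 8 than they are, and the direction of bias in the between-group difference is not fixed. Its size cannot be estimated, because the documents give neither relapse rates nor the share of relapses that would meet the trigger. The figures in the working show direction and possible scale under assumptions only. The affected results are secondary.

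**What to change.** Leave every decision about stopping treatment as it is, with the physician. Add to Withdrawal criteria that meeting a criterion does not in itself end data collection: every randomised participant who has not withdrawn consent keeps the day-10 assessment and the follow-up contacts to week 8. State that deterioration, infarction and arrhythmia are recorded and analysed both as outcomes and as adverse events. Reconcile Emergency unblinding with this, so that unblinded patients are also followed to week 8.

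The cost is protocol wording and a few extra contacts with patients who would otherwise have left. The visits, diary and case report form already exist. The change is worth making while enrolment continues, because values not collected cannot be recovered later.

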### Sample size

A previous study for *Guhong* injection in the treatment of angina pectoris [12] showed that the effective rate of the conventional treatment group (33 cases) was 81.82%, while that of the *Guhong* injection plus conventional treatment group (33 cases) was 93.94%. According to the literature, it was assumed that the efficiency rate of the *Guhong* injection group was from 81.82–93.94%, and the sample size was calculated based on the parameter *α* = 0.05 (bilateral test) and *β* = 0.2. By comparing the effectiveness rate of the two groups according to the following sample-size estimation formula:
$$ \mathrm{N}=\left[{\uppi}_{\mathrm{t}}\ \left(1-{\uppi}_{\mathrm{t}}\right)/\mathrm{k}+{\uppi}_{\mathrm{c}}\ \left(1-{\uppi}_{\mathrm{c}}\right)\right]\left(\ {\upmu}_{1-\upalpha /2}+{\upmu}_{1-\upbeta}\right)2/\left({\uppi}_{\mathrm{t}}-{\uppi}_{\mathrm{c}}\right), $$

we calculated that 111 patients should be recruited for each group. Taking into consideration an attrition rate of < 15%, the eligible participants in each group should be > 130. Ultimately, we determined the final sample size to be 130 (*N* = 260 in total).

